### Sample size calculation

In a phase III clinical trial conducted by Sakaida *et al.*
^18^ on the efficacy of tolvaptan in patients with cirrhosis with hepatic edema, weight losses were –0.44 kg (SD, 1.93) in the placebo group (*n*=80) and –1.95 kg (SD, 1.77) in the tolvaptan group (*n*=82). In a dose-ranging study of tolvaptan in patients with cirrhosis with hepatic edema conducted by Okita *et al*.^19^ weight losses were –0.36 kg (SD, 2.06) in the placebo group (n=25) and –2.3 kg (SD, 2.35) in the tolvaptan group (n=25). In other words, 1–2 kg of weight loss is expected with tolvaptan.

In our previous data, a postoperative weight gain of ~3 kg was observed patients with refractory ascites who underwent drainage of 5 ml/BW 1 kg on the first day after hepatectomy. As the same weight and ascites loss as in previous literature are expected to occur, it is assumed that the use of tolvaptan can limit postoperative weight gain to 2 kg. Assuming an SD of 2.0, an effect size of 0.5, a power of 0.9, and a significance level of 0.1, 25 cases are required; considering that the dropout rate is ~10%, 30 cases are set as the required number of cases.

### Interventions

#### Tolvaptan oral administration

For patients with ascites drainage ≥5 ml/BW 1 kg on postoperative day 1, tolvaptan 7.5 mg will be added to potassium canrenoate 200 mg (or spironolactone 50 mg) starting on postoperative day 2. Tolvaptan will be administered once daily in a glass of water. When a patient forgets to take a dose of tolvaptan, the patient will take tolvaptan immediately if it is within 4 h of the scheduled dose; if ≥4 h has passed, the patient will resume taking the drug as usual the next time. The dose may be reduced or discontinued if possible as the disease improves.

#### Concomitant diuretics

Potassium canrenoate 200 mg intravenously once daily or spironolactone 50 mg orally once daily will be the basic treatment on postoperative day 1. Similar to tolvaptan, potassium canrenoate can be reduced or discontinued as required as symptoms improve. If the ascites is difficult to control, potassium canrenolate or hurosemide may be added. Other concomitant therapies commonly used in daily practice are not restricted. The treatment duration for refractory ascites, including oral tolvaptan, should range from 2 weeks to 1 month.

### Follow-up and assessment of efficacy

#### Assessment tools

The maximum perioperative weight change will be the primary endpoint of this study. The secondary endpoints will include drainage volume, abdominal circumference, and urine output. Blood tests, chest radiography, and computed tomography (CT) will be used to evaluate the incidence of postoperative complications and changes in the improvement of postoperative pleural effusion. To assess patient safety, blood sodium and potassium levels and liver and renal functions will be evaluated.

#### Observation and examination schedule

Urine output, BW, and abdominal circumference will be measured daily until discharge. Preoperative BW should be measured within 7 days prior to surgery, and BW should be measured as soon as possible after waking up. Drainage volume should be measured daily until the drain is removed. The timing of the drain removal will be at the discretion of the attending physician. Blood tests will be performed daily until 7 days postoperatively, and after 10 days at the discretion of the attending physician. Preoperative blood tests should be performed within 90 days prior to surgery. Chest radiography will be performed within 90 days before surgery, immediately after surgery, and on first, third, fifth, and seventh postoperative days. CT will be performed according to the patient’s condition. After discharge, BW and abdominal circumference measurements, blood tests, and chest radiography will be performed during outpatient visits 30 and 90 days postoperatively. The patients will also be evaluated for adverse events. Observation will be completed 90 days postoperatively.

### Statistical analysis

The primary objective of the study will be to determine the efficacy and safety of tolvaptan therapy. For items observed as continuous values, the number of examples, number of missing examples, mean (median), SD (quartile), and range (minimum-maximum) will be calculated as summary statistics. For items observed as discrete values, the number of examples in each category and their percentages will be calculated as summary statistics. For safety evaluation, the number and percentage of adverse events will be calculated using the subjects for whom at least one research treatment has been performed as the analysis population. Statistical tests for the main analysis will be performed at a 5% significance level (two-sided).

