**Materials and methods::**

This is an open-label, single-arm phase I/II study. This study subject will comprise patients scheduled for hepatic resection of a liver tumor. Patients with refractory ascites after hepatic resection (drainage volume on postoperative day 1 ≥5 ml/body weight 1 kg/day) will be treated with tolvaptan. The primary endpoint will include the maximum change in body weight after hepatic resection relative to the preoperative baseline. The secondary endpoints will include drainage volume, abdominal circumference, urine output, postoperative complication rate (heart failure and respiratory failure), number of days required for postoperative weight gain because of ascites to decrease to preoperative weight, change in improvement of postoperative pleural effusion, total amount of albumin or fresh frozen plasma transfusion, type and amount of diuretics used, and postoperative hospitalization days.

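### The sample size assumes a significance level of 0.1 for 90% power, but the main test is set at 5% two-sided, where the planned patients give about 67–75% power

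*Protocol article*

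**What the plan says.** Two sections of the protocol article give a significance level for the primary question.

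- **Sample size calculation.** The sponsor's earlier data supply the reference: "a postoperative weight gain of ~3 kg was observed" in comparable patients. The working assumption is that "the use of tolvaptan can limit postoperative weight gain to 2 kg". The calculation then reads "Assuming an SD of 2.0, an effect size of 0.5, a power of 0.9, and a significance level of 0.1, 25 cases are required". Finally, "considering that the dropout rate is ~10%, 30 cases are set as the required number of cases". It does not say whether 0.1 is one-sided or two-sided.
- **Statistical analysis.** "Statistical tests for the main analysis will be performed at a 5% significance level (two-sided").

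The primary endpoint, under Study objectives and endpoints, is the maximum change in body weight from the preoperative value. That is the quantity the sample size section plans for, so both levels concern the same comparison. No sentence restricts the 5% level to secondary endpoints or explains why planning used a different level.

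**The concern.** A power statement holds only for the level at which the test is run. The 90% was worked out at 0.1 and the test is declared at 0.05 two-sided, so the trial does not have its stated power for its declared test.

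Two things are at stake. First, a real 1 kg benefit would be missed far more often than the plan says. The Discussion makes a phase III trial conditional on positive results, without defining positive. Second, with two levels on paper in an open-label, single-arm trial, a two-sided p-value between 0.05 and 0.10 could be called a success by one section and a failure by the other.

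**Working it through.** **Inputs, all from the Sample size calculation unless noted**

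- Reference mean gain 3 kg; expected mean on tolvaptan 2 kg; SD 2.0 kg.
- Standardised effect d = (3 − 2)/2.0 = 0.5, which agrees with the stated effect size.
- Planned power 0.9; planning level 0.1, sidedness not given.
- Required 25; enrolled 30; dropout about 10%, so 30 × 0.9 = 27 evaluable.
- Level of the main test: 0.05 two-sided (Statistical analysis).
- Design: single arm (abstract, Materials and methods), hence a one-sample comparison with a fixed reference. A two-sample formula with these inputs gives 53 to 85 per arm, depending on level and sidedness, so it cannot be the source of 25.

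**Step 1. Reproduce the plan's 25.** Normal approximation: n = ((z_α + z_power)/d)².

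- 0.1 one-sided, 90% power: ((1.282 + 1.282)/0.5)² = 26.3, so 27 (exact t-test: 28).
- 0.1 two-sided, 90% power: ((1.645 + 1.282)/0.5)² = 34.3, so 35 (exact t-test: 36).
- 0.1 two-sided, 80% power: ((1.645 + 0.842)/0.5)² = 24.7, so 25 (exact t-test: 27).

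With 90% power, only a one-sided 0.1 comes near 25. It also fits the enrolment figure, since 27/0.9 = 30. A two-sided 0.1 gives 25 only if power is 80%, which is not what the section states.

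**Step 2. Power at the declared level.** Normal approximation: power = Φ(d√n − 1.960). For n = 25: 0.5 × 5 − 1.960 = 0.540, and Φ(0.540) = 0.705. The exact figures use the noncentral t distribution with n − 1 degrees of freedom and noncentrality d√n.

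| Evaluable n | 5% two-sided, t-test | 5% two-sided, normal | 10% two-sided, t-test | 10% one-sided, t-test |
|---|---|---|---|---|
| 25 | 67.0% | 70.5% | 78.3% | 88.0% |
| 27 | 70.6% | 73.8% | 81.2% | 89.9% |
| 30 | 75.4% | 78.2% | 84.8% | 92.2% |

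**Step 3. Number needed for 90% power at 5% two-sided.** ((1.960 + 1.282)/0.5)² = 42.0, which rounds up to 43; the exact t-test needs 44. With 10% dropout, 43/0.9 = 47.8 and 44/0.9 = 48.9, so 48 to 49 enrolled.

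**Step 4. Chance of missing a true 1 kg effect.** With 27 evaluable patients at 5% two-sided: 1 − 0.706 = 0.294, or about 29%, against the planned 10%.

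**The case against.** The best defence is that the sample size section should be read on its own terms. It states no sidedness, and a one-sided 0.1 gives 27 by the normal approximation, 88% power at 25 and exactly 30 after dropout. On that reading 25 is a near miss rather than an error. This stands, and the figure of 25 is not the main defect. The reading does, however, widen the gap between the sections: in the direction of benefit, planning uses 0.10 and the declared test uses 0.025, a fourfold difference. It also widens the disputed range of two-sided p-values from 0.05–0.10 to 0.05–0.20.

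It can also be said that the Statistical analysis section governs and is the stricter of the two, so the false-positive risk is not raised. That is correct. The damage is to the stated power and to the clarity of the success criterion.

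The article names neither the test nor the null value, so the power figures rest on an inference. That is also true. But the single arm, the 3 kg reference and the effect size of 0.5 point to a one-sample comparison, and the normal approximation (71–78%) leads to the same conclusion as the t-test (67–75%).

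A lenient level is acceptable in phase I/II. It is, but the main test must then be declared at that level. Nor would a separate analysis plan remove the problem: whichever level it chose, one of these two sections would still be wrong.

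**Conclusion.** The concern holds. The two sections give incompatible levels for the main analysis, and no choice of sidedness reconciles them. At the declared 5% two-sided level, power is about 71% with the expected 27 evaluable patients (67% with 25, 75% with 30), not 90%. Even with no dropout at all, the planned enrolment falls well short.

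This assumes a one-sample t-test against a fixed 3 kg, a true mean of 2 kg, an SD of 2.0 kg and 10% dropout. The existence of the conflict depends on none of these; only its size does. It should be corrected before analysis, because it concerns how the primary result will be judged.

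**What to change.** State one level and one sidedness, identically in both sections, before any outcome is analysed. There are three ways to do it:

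1. **Keep 5% two-sided and restate the power** as about 71% with 27 evaluable patients (75% with 30), naming the one-sample test and the 3 kg reference on which that rests. This leaves the declared criterion unchanged and needs no extra patients. The cost is a less favourable power statement.
2. **Declare the main test one-sided at 0.10 as a screening level**, with about 90% power at 27 evaluable. This matches the apparent basis of the sample size, but it loosens the declared criterion in an open-label trial whose registration period began in March 2023. The amendment should therefore be dated, give its reason and confirm that no outcome data had been analysed.
3. **Keep both 5% two-sided and 90% power**, which requires 44 evaluable patients, or 49 enrolled at 10% dropout, instead of 30.

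The first is the cleanest. The first two each cost one sentence in each section; the third costs 19 more patients (49 − 30).

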## Discussion

This trial will evaluate the efficacy and safety of tolvaptan prophylaxis for refractory ascites after hepatic resection. The primary endpoint will be perioperative maximum weight change. The secondary endpoints will include drainage volume, abdominal circumference, urine output, postoperative complication rate, number of days required for postoperative weight gain because of ascites to decrease to preoperative weight, change in improvement of postoperative pleural effusion, total amount of albumin or FFP transfusion, type and amount of diuretics used, and postoperative hospitalization days.

Tolvaptan is an orally selective vasopressin type 2 receptor antagonist that inhibits water reabsorption by decreasing aquaporin 2 expression in the collecting duct, thereby promoting free water excretion without increasing sodium excretion^26,27^. It is expected to be renal protective by maintaining renal blood flow during diuresis without activating the renin-angiotensin-aldosterone system^28,29^.

In 2013, a Japanese clinical trial approved the use of tolvaptan in combination with a conventional diuretic for refractory ascites^32^. Subsequently, the efficacy of tolvaptan for refractory ascites was confirmed regardless of serum albumin levels^18^, and the Japanese Society of Gastroenterology recommended early administration of tolvaptan before increasing the dose of furosemide or spironolactone^33^.

Some reports have indicated that tolvaptan improves the long-term prognosis in patients with refractory ascites. Hiramine *et al.*
^22^demonstrated that the survival rate was significantly higher in the tolvaptan using group than in the tolvaptan nonusing group in patients with hepatic ascites. A meta-analysis also demonstrated that tolvaptan significantly improved the overall survival of patients with cirrhosis and refractory ascites^29^. Tolvaptan has been reported to reduce the incidence of acute kidney injury in patients with hepatic ascites^24^. Acute kidney injury has also been reported to be induced by diuretics^34^, and the concomitant use of tolvaptan is important for renal protection. Based on these studies, we hypothesized that early administration of tolvaptan would be effective for the treatment of refractory ascites after hepatic resection.

As there are no reports demonstrating the efficacy of tolvaptan prophylaxis for refractory ascites after hepatic resection, we will analyze the safety and efficacy of this therapy in this clinical trial. We expect that these findings will lead to future phase III trials and provide valuable indications for the selection of treatments for refractory postoperative ascites.

This study protocol has several limitations. Firstly, it is a single-arm study, not a comparative study. Second, some confounding factors cannot be completely ruled out. Postoperative ascites may be influenced by the volume of resected liver, liver damage, and operative time. If positive results are obtained in this phase I/II study, we plan to conduct a phase III study including a control group to control for confounding factors. Within the limitations of this study, we believe that this study to evaluate the efficacy and safety of tolvaptan in patients with refractory ascites after hepatic resection is a useful tool that can lead to a phase III study.

## Ethics approval and consent to participate

The protocol was approved by the Certified Committee for Regenerative Medicine, Hiroshima

University, Japan (CRB2022-0018).

## Consent for publication

Informed consent will be obtained from all patients before inclusion in this study.

## Research registration unique identifying number (UIN)

The trial was prospectively registered at Japan Registry of Clinical Trials (jRCTs061220114).

## Availability of data and materials

No datasets were generated or analyzed during the current study. All relevant data from this study will be made available upon study completion.
